#### **9.2.4. Formula Intake Volume**

The volume of formula consumed in ounces is recorded at visits 1, 2, 3, 5, 7, and 9. An initial 3-day Formula/Diet Record will be recorded for 3 days following the first study visit. The remainder of 3-day Formula/Diet Records will be recorded for 3 days prior to each subsequent scheduled study visit. Records will be assigned to 24-hour windows. The average daily volume (oz/day) will be calculated by averaging the 24-hour windows with sufficient information. 24-hour windows that have less than 4 feeding records will not be included when calculating the average daily volume. The average daily volume will be summarized by formula group and visit using descriptive statistics. A two-sample t-test will be used to test a difference between formula groups at each visit with 95% confidence intervals and p-values presented.

Average daily formula intake (oz/kg/day) and average daily formula intake (mL/kg/day) will also be summarized by formula group and visit using descriptive statistics.

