**Secondary Efficacy Objective:**

Compare the formula intake volume between the formula groups.

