### **2.2.2. Secondary Efficacy Objective**

The secondary efficacy objective is to compare the formula intake volume between the formula groups (BBN-102 w/o OPN vs Brand Formula).

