### **6.8. Adjustments for Covariates**

Adjustments for sex, age at enrollment, baseline values, formula, visit, pooled site, formula by pooled site interaction, and formula by visit interaction will be made for statistical analyses. If the model does not converge when using all these covariates, then the formula by pooled site interaction term will be dropped from the model.

Some of the sites have very few subjects. All sites in the same state will be grouped together and then states will be grouped together geographically into a new pooled site variable.

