## 9.1. Primary Efficacy Analysis

The primary efficacy endpoint, mean daily weight gain (g/day) over the 16-week study period and at each study visit, will be calculated as (average weight in grams at each study visit – average weight in grams at baseline visit)/number of days since baseline visit. The weight is measured a minimum of two times at each study visit (a third weight is measured if the first two do not meet the threshold specified in the protocol). If two measurements are taken, then the average of the two will be used in the preceding formula. If there are more than two measurements, then the two measurements that are the closest will be averaged and used in the preceding formula. If three measurements are equidistant, then the lower two measurements will be averaged and used in the preceding formula. If there are less than 2 measurements recorded, then the average weight measurement will be set to missing. This average weight measurement will be used in the calculation for mean daily weight gain above. Descriptive statistics of the mean daily weight gain will be presented by visit and formula group. Mean daily weight gain at visit 9 (Day 120) will be compared between BBN-102 w/o OPN and the Brand Formula with a mixed-effect model for repeated measures (MMRM). The test for non-inferiority of the primary efficacy endpoint will have the following hypotheses:

H0: The difference (BBN-102 w/o OPN – Brand Formula) in mean daily weight gain between the formula groups is less than or equal to -3 g/day at visit 9 (Day 120).

H1: The difference (BBN-102 w/o OPN – Brand Formula) in mean daily weight gain between the formula groups is greater than -3 g/day at visit 9 (Day 120).

Formula groups will be compared using a MMRM with sex, age at enrollment, baseline value, formula, visit, pooled site, formula by pooled site interaction, and formula by visit interaction as factors. The covariance matrix will be chosen based on the Akaike Information Criterion (AIC) to choose the covariance matrix that best fits the model. Non-inferiority will be determined if the lower limit of the two-sided 95% CI for the difference (BBN-102 w/o OPN – Brand Formula) in least square means is greater than -3, assuming a non-inferiority margin of 3 g/day.

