## 9.2. Secondary Efficacy Analysis

The following secondary endpoints (growth velocities, growth z-scores, growth measurements, and formula intake) are of interest and will be analyzed in a similar method as the primary efficacy endpoint. Each secondary endpoint will be analyzed using the Hochberg step-up multiple testing procedure to control for the familywise error rate at level  $\alpha$ . Statistical difference of formula groups will be tested using Hochberg corrected p-values. The following secondary efficacy endpoints will be analyzed:

Growth velocities:

- Mean daily length gain (mm/day) at visit 9 (Day 120)
- Mean daily head circumference gain (mm/day) at visit 9 (Day 120)

Growth Z-scores:

- Mean weight-for-age z-score at visit 9 (Day 120)
- Mean length-for-age z-score at visit 9 (Day 120)
- Mean weight-for-length z-score for age at visit 9 (Day 120)
- Mean head circumference-for-age z-score at visit 9 (Day 120)

Growth measurements:

- Mean weight (g) at visit 9 (Day 120)
- Mean length (cm) at visit 9 (Day 120)
- Mean head circumference (cm) at visit 9 (Day 120)

The average daily volume of formula intake will be compared between formula groups at visits 1, 2, 3, 5, 7, and 9.

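### Formula intake, the only stated secondary efficacy objective, is tested by six t-tests without covariates, in conflict with the SAP's own rule of an adjusted repeated-measures model

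*Supplement*

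**What the plan says.** SAP V4 section 2.2.2 states: "The secondary efficacy objective is to compare the formula intake volume between the formula groups". Protocol version 5.2 section 5 gives the same single secondary efficacy objective. Growth measures are secondary endpoints too, but no secondary efficacy objective names them.

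On how intake is to be analysed, the SAP gives two instructions:

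- Section 9.2 lists the secondary endpoints, formula intake by name, and says they "will be analyzed in a similar method as the primary efficacy endpoint". Section 9.1 makes the primary analysis an MMRM. Section 6.8 sets the general covariate rule: "Adjustments for sex, age at enrollment, baseline values, formula, visit, pooled site", plus two interaction terms.
- Section 9.2.4 says of intake in oz/day: "A two-sample t-test will be used to test a difference between formula groups at each visit". It names no covariates, no model across visits and no reason for departing from 9.2. Intake per kg body weight is also planned, but only as descriptive summaries.

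Section 9.2 fixes the number of comparisons: "The average daily volume of formula intake will be compared between formula groups at visits 1, 2, 3, 5, 7, and 9". Sections 6.7 and 9.2 place formula intake under the Hochberg procedure. Section 9.2.4 does not mention correction.

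**The concern.** A programmer could follow 9.2 with 6.8, or 9.2.4, and would get different estimates and p-values for the one stated secondary efficacy objective. The nine growth endpoints each have an adjusted MMRM at Day 120. Intake alone among the secondary efficacy endpoints has no covariates, no repeated-measures model and no designated time point.

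Covariates matter more here than in an ordinary two-arm trial. Most Brand infants were randomized in phase one and every BBN-102 infant in phase two, so randomization does not balance age, size or site for most of the comparison. Section 9.1.2 checks the similarity of the two enrollment periods for weight gain only, not for intake.

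At stake are precision, measured imbalance left in the estimate, and six answers to one question with none named as the answer.

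**Working it through.** **1. The plan's own figures.** The SAP gives no standard deviation, power or sample size for intake. Its phase-two power figure concerns weight gain (104 Brand, 64 BBN-102, SD 6.0 g/day, margin 3 g/day, one-sided 0.025). SE = 6.0 × sqrt(1/104 + 1/64) = 0.953, and 3/0.953 − 1.96 = 1.19, so power is 88.2% against a stated figure of about 90%. This reproduces well enough and has no bearing on intake.

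**2. The sections side by side.**

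| Feature | 9.2 with 9.1 and 6.8 | 9.2.4 |
|---|---|---|
| Method | MMRM | t-test at each visit |
| Sex (stratification factor), age, pooled site | adjusted | not used |
| Correlation between visits | modelled | ignored |
| Result | one contrast, Day 120 in the primary analysis | six, none designated |

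The primary model cannot be copied unchanged. Section 6.3 defines baseline as a value recorded before the first feeding of assigned formula. The first intake record covers the 3 days after Visit 1, when study formula is already being fed, so intake has no baseline value.

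**3. Who is compared.** Section 5 of the SAP: 129 phase-one and about 10 phase-two Brand infants, 129/139 = 93% from phase one. All of the roughly 86 BBN-102 infants come from phase two.

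**4. Precision.** If the covariates explain a share R² of intake variance and are roughly balanced between groups, the confidence interval shrinks by the factor sqrt(1 − R²), equivalent to 1/(1 − R²) times as many infants. The documents give no R², so the values are assumed:

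| R² | CI width ratio | Equivalent sample |
|---|---|---|
| 0.05 | 0.97 | 1.05 |
| 0.15 | 0.92 | 1.18 |
| 0.25 | 0.87 | 1.33 |

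**5. Multiplicity.** Six independent tests at 0.05 with no correction give 1 − 0.95⁶ = 26.5%. The table simulates six equally correlated tests (200,000 runs; the correlations are assumed):

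| Correlation | No correction | Hochberg over the six |
|---|---|---|
| 0 | 26.6% | 4.9% |
| 0.3 | 24.1% | 4.6% |
| 0.5 | 20.8% | 4.1% |
| 0.7 | 16.5% | 3.4% |
| 0.9 | 10.8% | 2.4% |

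The SAP states Hochberg, so the right-hand column applies if all six tests are corrected.

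**6. The undefined family.** Growth supplies 2 velocities + 4 z-scores + 3 measurements = 9 tests. The strictest Hochberg threshold is 0.05/15 = 0.0033 if the six intake tests join them, 0.05/10 = 0.005 if one intake contrast joins them, and 0.05/6 = 0.0083 if intake forms its own family. In a shared family, the choice also changes the corrected p-values for growth.

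**The case against.** The strongest reply is that 9.2.4 is the specific, executable instruction, while the sentence in 9.2 is general and 6.8 reads as a model specification (it includes visit terms and a rule for non-convergence). The SAP uses tests without covariates elsewhere: t-tests for inflammation markers and Fisher's exact tests for adverse events of special interest. This has some force, but 9.2 lists formula intake by name, so the conflict stands.

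A t-test at each visit is also valid between concurrently randomized groups, and if anything slightly conservative under sex stratification. That is true, but most controls here are not concurrent. Eligibility does bound age at entry (at most 14 days) and size (5th to 95th percentiles), so imbalance is possible rather than shown. Adjustment for measured covariates does not remove enrollment-period effects, which are a separate matter.

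Two stronger readings are tempting and should not be drawn:

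- A reader might infer a 16-25% chance of a false positive from six tests at 0.05. That describes a procedure the SAP does not plan, because 6.7 and 9.2 place intake under Hochberg.
- A reader might infer that infant size is ignored altogether. Section 9.2.4 reports intake per kg by group and visit. It is only not tested, which is defensible if the divisor is concurrent weight, since the formula may affect that weight.

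On missing diaries, each t-test uses only infants with usable data at that visit, whereas an MMRM also draws on their other visits. The documents give no figure for how many infants this concerns.

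**Conclusion.** The point holds as a worthwhile improvement, not as a finding that the planned test is invalid. The SAP contradicts itself on the analysis of its only stated secondary efficacy objective, and the version in 9.2.4 is the weaker one. It discards the stratification factor and the repeated measures and leaves measured imbalance between largely non-concurrent groups in the estimate.

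The size is modest and rests on an assumed R²: a confidence interval 3-13% narrower for R² of 5-25%, with less gain if the covariates are unbalanced between groups. The direction and amount of any imbalance cannot be known from the documents. The multiplicity question is limited to whether intake counts as six tests or one and in which family.

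**What to change.** In 9.2.4, replace the six t-tests with one MMRM of daily intake (oz/day) on formula, visit, formula by visit, sex, age at enrollment, baseline weight and pooled site. Do not use Visit 1 intake as a covariate, because it is recorded after study feeding starts. This list omits the formula by pooled site interaction named in 6.8, so the SAP should say so.

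Name one contrast in advance, for example Day 120 to match the other secondary efficacy endpoints, and enter only that contrast in the Hochberg family. State in 6.7 which tests make up the family. Report by-visit estimates with confidence intervals as supportive. Keep per-kg intake descriptive or supportive.

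The cost is SAP wording in 6.7, 9.2 and 9.2.4 and some programming of a model close to those planned for growth. No new data are needed.

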### **9.3. Exploratory Analysis**

The following exploratory endpoints will be analyzed:

#### **Markers of Inflammation**

- Mean value for tumor necrosis factor-alpha at visit 9 (Day 120)
- Mean value for interleukin 2 at visit 9 (Day 120)
- Mean value for interleukin 4 at visit 9 (Day 120)
- Mean value for interleukin 5 at visit 9 (Day 120)
- Mean value for interleukin 6 at visit 9 (Day 120)
- Mean value for interleukin 8 at visit 9 (Day 120)
- Mean value for interleukin 10 at visit 9 (Day 120)
- Mean value for interleukin 12 at visit 9 (Day 120)
- Mean value for interleukin 13 at visit 9 (Day 120)
- Mean value for interleukin 17 at visit 9 (Day 120)
- Mean value for interleukin 2 receptor at visit 9 (Day 120)
- Mean value for interleukin 1 beta at visit 9 (Day 120)
- Mean value for interferon gamma at visit 9 (Day 120)

### 9.3.1. Markers of Inflammation

A single blood sample (of at least 0.5 milliliters but not more than 0.8 milliliters) will be collected from each subject via heel stick at the last study visit (visit 9, Day 120) to assess markers of inflammation (tumor necrosis factor-alpha, interleukin 2, 4, 5, 6, 8, 10, 12, 13, and 17; interleukin 2 receptor, interleukin 1 beta, and interferon gamma). Biomarker values that are below the lower limit of detectability will be set to that lower limit value (for example, < 5 ng/mL will be replaced with 5 ng/mL). Summary statistics for these biomarkers will be summarized separately by formula group. Formula groups will be compared using a two-sample t-test with 95% confidence intervals and p-values to test the following hypotheses:

H0: The mean values for the marker of inflammation for each formula group is equal.

H1: The mean values for the marker of inflammation for each formula group is not equal.

No adjustment for alpha will be made for these exploratory endpoints.

## 10. Pharmacokinetic Analysis

No pharmacokinetic analysis is planned for this study.

## 11. Safety Analysis

All safety analysis will be based on the Safety Population. Analysis using the Safety population will be based on the formula the infant is given.

The gastrointestinal tolerance safety endpoints will be summarized by study visits. The protocol schedule of assessment lists target visit days that occur every 15 days and associated tests to be conducted on these visits and also specify associated visit windows (+/- 3 days) for these visits. However, it is not uncommon for subjects to have visits outside the protocol specified visit windows due to various reasons. Because of this, analysis visits and windows are specified below to include as much data as possible in the analyses. While presenting summaries of data by visit, analysis visits will be used according to the windows specified below. Using the analysis visits and windows allow for more comparable comparisons of test results which are closest to the protocol specified target visits and time on study formula while correcting for possible issues that occurred during the study.

| Analysis Visit | Target Day | Window |
|----------------|------------|--------|
| Page 24        |            |        |

|   |     |           |
|---|-----|-----------|
| 1 | 0   | N/A       |
| 2 | 15  | 8 – 22    |
| 3 | 30  | 23 – 37   |
| 4 | 45  | 38 – 52   |
| 5 | 60  | 53 – 67   |
| 6 | 75  | 68 – 82   |
| 7 | 90  | 83 – 97   |
| 8 | 105 | 98 – 112  |
| 9 | 120 | 113 – 134 |

Analysis relative day (ADY) will be derived and used to determine the appropriate analysis visit. The subject's randomization date (ADY = -1) will be used to calculate the treatment start day (ADY = 1) and the analysis relative day for each study visit. ADY will be used to compare to the analysis visit target day to identify the analysis visit. If more than one visit falls within a window, then the visit closest to the target day will be used in the analysis (ANL02FL = Y). If more than one visit falls within a window and they are the same distance to the target day, then the latest visit will be used in the analysis. Unscheduled assessments will be assigned to the associated analysis visit based on date and time of assessment.

### 11.1. Adverse Events

Adverse events (AE) summaries will only consider Treatment Emergent Adverse Events (TEAEs). TEAEs are defined as those adverse events with date of onset after formula intake and those existing adverse events that worsened during the study. If it cannot be determined whether the AE is treatment emergent due to a missing or incomplete (partial) onset date, the AE will be considered treatment emergent. Verbatim terms entered into the clinical database via the EDC system will be mapped to preferred terms and system organ classes using the Medical Dictionary for Regulatory Activities (MedDRA), version 23.0.

Each AE summary will be displayed by formula group. Summaries that are displayed by system organ class and preferred terms will be ordered by descending order of incidence of system organ class and preferred term within each system organ class. Summaries of the following types will be presented:

- Overall summary of the TEAEs which contain an overview of each item below.
- Subject count and incidence rate of TEAEs by MedDRA system organ class (SOC) and preferred term (PT).

- Subject count and incidence rate of TEAEs by MedDRA SOC, PT and highest severity. At each level of subject summarization, a subject is classified according to the highest severity if the subject reported one or more events.
- Subject count and incidence rate of TEAEs by MedDRA SOC, PT and closest relationship to study drug (Related/Not Related). Related AEs are those reported as “Related” or “Possibly Related”. At each level of subject summarization, a subject is classified according to the closest relationship if the subject reported one or more events. Adverse events with missing relationship will be considered related for this summary.
- Subject count and incidence rate of Serious TEAEs by MedDRA SOC and PT.
- Subject count and incidence rate of TEAEs leading to study discontinuation by MedDRA SOC and PT.

#### 11.1.1. Adverse Events of Special Interest

An overall summary of number and percentage of infants with any physician-reported AE of special interest will be presented by formula group.

Subject count and incidence rate by highest severity and by causality will be presented for all physician-reported AEs of special interest, A by-patient listing of all AEs of special interest will be provided.

Standardized definitions for common AEs that may or may not be related to formula tolerance (stooling, spit-up, vomiting, GERD, crying, skin issues) were provided to all investigators. Comparisons between formula groups of the incidence of these AEs of special interest will be tested using Fisher’s Exact tests.

Time to first gastrointestinal event will be analyzed using Kaplan-Meier method by formula group. Kaplan-Meier estimates of the 25th, 50th, and 75th percentiles and the 95% confidence intervals of the median will be provided for each formula group.

| ADVERSE EVENT                    | DEFINITION                                                         |
|----------------------------------|--------------------------------------------------------------------|
| Stooling Issues           |                                                                    |
| Difficulty having bowel movement | Crying, fussing, or turning red when having a bowel Movement       |
| Hard stools                      | Healthcare professional diagnosis; pellet or hard rock-like Stools |
| Constipation                     | Less than 3 bowel movements in 7 days                              |
| Acute diarrhea                   | Runny or watery stools for less than 2 weeks                       |

|                                        |                                                                                                                                                                                                                                                                                                                                                                                                                                                                                                                                     |
|----------------------------------------|-------------------------------------------------------------------------------------------------------------------------------------------------------------------------------------------------------------------------------------------------------------------------------------------------------------------------------------------------------------------------------------------------------------------------------------------------------------------------------------------------------------------------------------|
| Chronic diarrhea                       | Runny or watery stools for more than 2 weeks or $\geq 3$ separate episodes of acute diarrhea in 2 weeks                                                                                                                                                                                                                                                                                                                                                                                                                             |
| Spit-up, Vomiting, GERD issues  |                                                                                                                                                                                                                                                                                                                                                                                                                                                                                                                                     |
| Regurgitation                          | Milk comes up into mouth but never out of mouth AND infant DOES NOT arch his/her back as if in pain, stop drinking even if hungry, or cry, wheeze, or cough related to feedings                                                                                                                                                                                                                                                                                                                                                     |
| Infantile spit up                      | Milk comes out of the mouth after feeding (typically non-forceful), and the amount that comes out is less than half of the feeding volume; non-projectile                                                                                                                                                                                                                                                                                                                                                                           |
| Vomiting                               | Milk comes out of the mouth after feeding (typically forceful), and the amount that comes out is more than half of the feeding volume                                                                                                                                                                                                                                                                                                                                                                                               |
| Gastroesophageal Reflux Disease (GERD) | Baby arches his/her back as if in pain, stop drinking even if hungry, or cry, wheeze or cough related to feedings (with or without milk coming up into mouth)                                                                                                                                                                                                                                                                                                                                                                       |
| Crying issues                   |                                                                                                                                                                                                                                                                                                                                                                                                                                                                                                                                     |
| Crying/Neonatal abnormal crying        | Infant cries for 3 or more hours per day                                                                                                                                                                                                                                                                                                                                                                                                                                                                                            |
| Infantile colic/Infant colic           | Infant cries inconsolably for 3 or more hours per day, at least 3 days per week, AND for at least 3 weeks                                                                                                                                                                                                                                                                                                                                                                                                                           |
| Skin issues                     |                                                                                                                                                                                                                                                                                                                                                                                                                                                                                                                                     |
| Diaper rash                            | 
Contact/irritant dermatitis in the diaper area, with erythema and/or skin breakdown on the exposed convex skin surface (rate as Mild, Moderate, Severe using definitions outlined below)
 
Mild: Baby has an area of pinkness in the diaper area
 Moderate: Baby has definite pinkness in a large area with some small areas of definite redness
 Severe: Baby has intense redness over a large area of the perianal region, or any area of redness with skin breakdown in the diaper area
 |
| Atopic dermatitis/Eczema               | 
Any skin lesions, not in the diaper area. Score for any erythema, edema/papulation, and/or excoriation on scale from 0-3 each (9 points max). For each item, 0 = none, 1 = mild, 2 = moderate, 3 = severe.
 
Mild: 1 or 2 points
 Moderate: 3 to 5 points
                                                                                                                                                                                                                                             |

|  |                              |
|--|------------------------------|
|  | Severe: 6 to 9 points |
|--|------------------------------|

